# Implementation and evaluation of a large-scale postpartum family planning program in Rwanda: study protocol for a clinic-randomized controlled trial

**DOI:** 10.1186/s13063-022-06261-5

**Published:** 2022-04-22

**Keywords:** Postpartum, Family planning, Contraception, Birth spacing, Implementation, Rwanda, Stepped-wedge randomized trial

## Abstract

**Background:**

Though the Rwandan Ministry of Health (MOH) prioritizes the scale-up of postpartum family planning (PPFP) programs, uptake and sustainability of PPFP services in Rwanda are low. Furthermore, highly effective long-acting reversible contraceptive method use (LARC), key in effective PPFP programs, is specifically low in Rwanda. We previously pilot tested a supply-demand intervention which significantly increased the use of postpartum LARC (PPLARC) in Rwandan government clinics. In this protocol, we use an implementation science framework to test whether our intervention is adaptable to large-scale implementation, cost-effective, and sustainable.

**Methods:**

In a type 2 effectiveness-implementation hybrid study, we will evaluate the impact of our PPFP intervention on postpartum LARC (PPLARC) uptake in a clinic-randomized trial in 12 high-volume health facilities in Kigali, Rwanda. We will evaluate this hybrid study using the RE-AIM framework. The independent effectiveness of each PPFP demand creation strategy on PPLARC uptake among antenatal clinic attendees who later deliver in a study facility will be estimated. To assess sustainability, we will assess the intervention adoption, implementation, and maintenance. Finally, we will evaluate intervention cost-effectiveness and develop a national costed implementation plan.

**Discussion:**

Adaptability and sustainability within government facilities are critical aspects of our proposal, and the MOH and other local stakeholders will be engaged from the outset. We expect to deliver PPFP counseling to over 21,000 women/couples during the project period. We hypothesize that the intervention will significantly increase the number of stakeholders engaged, PPFP providers and promoters trained, couples/clients receiving information about PPFP, and PPLARC uptake comparing intervention versus standard of care. We expect PPFP client satisfaction will be high. Finally, we also hypothesize that the intervention will be cost-saving relative to the standard of care. This intervention could dramatically reduce unintended pregnancy and abortion, as well as improve maternal and newborn health. Our PPFP implementation model is designed to be replicable and expandable to other countries in the region which similarly have a high unmet need for PPFP.

**Trial registration:**

ClinicalTrials.gov NCT05056545. Registered on 31 March 2022.

## Administrative information

Note: The numbers in curly brackets in this protocol refer to SPIRIT checklist item numbers. The order of the items has been modified to group similar items (see https://www.equator-network.org/reporting-guidelines/spirit-2727-statement-defining-standard-protocol-items-for-clinical-trials/).

## Introduction

### Background and rationale {6a}

Uptake and sustainability of postpartum family planning (PPFP) services in Rwanda are low [1]. The Rwandan Demographic Health Survey (DHS) estimates that 51% of women have an unmet need for PPFP, which is higher than the unmet need during non-postpartum periods [2]. Long-acting reversible contraceptives (LARCs), including the copper intrauterine device (IUD) and hormonal contraceptive implant, are fundamental to PPFP programs. LARCs are highly effective and are the only reversible methods that may be safely used in the early postpartum period by breastfeeding women. As in most countries, postpartum use of long-acting reversible contraceptives (PPLARC) is low in Rwanda: among contracepting postpartum women, 8% use contraceptive implants and < 1% use the intrauterine device (IUD) [3, 4].

To address the high unmet need for PPFP and PPLARC in Rwanda, in 2017–2018, our research group worked closely with the Rwanda Ministry of Health (MOH) to develop and pilot test a theory-based, multi-level intervention targeting PPFP supply and demand in five government health facilities in Kigali, the capital. We trained government clinic providers to promote and provide PPFP methods, and we developed an educational counseling flipchart which detailed all PPFP options (PPLARC, injectables, pills, etc.) which was provided to 12,068 pregnant and postpartum women/couples in health facilities and the surrounding community. During our pilot, LARC uptake up to 6 weeks after delivery increased significantly (with 3372 PPIUD inserted representing a 2710% increase compared to the 6 months prior to our pilot, and 1252 implants inserted representing a 178% increase compared to the 6 months prior to our pilot), PPFP feasibility and acceptability were high among providers and clients, and side-effects were rare [5, 6].

While our short pilot was highly impactful in increasing PPFP uptake, much remains unknown: Is our PPFP intervention scalable without sacrificing quality? Will the inclusion of husbands, 85% of whom attend the first antenatal visit with their wives, increase PPLARC acceptability and uptake? Does the use of a Happy Client model of peer testimonial or PPFP promotions delivered by community health workers (CHW) increase intervention effectiveness? Is the intervention cost-effective? What demand creation strategies are most cost-effective? Is the intervention sustainable?

We now will conduct a type 2 effectiveness-implementation hybrid study [7, 8] to test the hypothesis that our PPFP intervention is adaptable to large-scale implementation, cost-effective, and sustainable. This intervention could dramatically reduce unintended pregnancy and abortion and improve birth spacing and maternal and newborn health in Rwanda.

### Objectives {7}

Aim 1: Implement the intervention in 12 high-volume health facilities: Guided by the Consolidated Framework for Implementation Research [9, 10], we will engage stakeholders and assess facility organizational readiness prior to implementation. No PPFP activities are currently taking place in these facilities. We will implement the PPFP intervention in a clinic-randomized stepped-wedge design. We expect to deliver PPFP promotional counseling to over 21,000 pregnant or postpartum women/couples.

Aim 2: Evaluate intervention effectiveness and implementation: The RE-AIM framework [11] will guide the outcome evaluation. We hypothesize that the intervention will significantly increase the number of stakeholders engaged, PPFP providers and promoters, couples/clients receiving information about PPFP, and LARC uptake comparing intervention versus standard of care. We expect PPFP client satisfaction will be high, and side effects will be rare. The independent effectiveness of each demand creation strategy on LARC uptake will be estimated. We assess the measures of intervention adoption, implementation, and maintenance at the patient, provider, and stakeholder levels to assess the intervention sustainability.

Aim 3: Evaluate intervention cost-effectiveness and cost-utility: We employ standard methods [12, 13] to estimate the costs and incremental cost-effectiveness and cost-utility of the intervention relative to the standard of care from the societal perspective. The cost-effectiveness of each demand creation strategy will be estimated. We hypothesize that the intervention will be cost-saving relative to the standard of care. A costed implementation plan will be developed to guide Rwandan MOH decision-making for the nationwide roll-out of PPFP services.

### Trial design {8}

We will implement the intervention in 12 facilities in a clinic-randomized stepped-wedge design. The stepped-wedge design will ensure that each facility receives the intervention over time and provides its own standard of care control, limiting temporal bias. Facilities are high-volume and have similar client volume and staffing-to-patient ratios. Each clinic will be randomized using the SAS random number generator (SAS Institute v9.4, Cary, NC). The allocation ratio will be 1:1. This is a superiority trial.

## Methods: participants, interventions, and outcomes

### Study setting {9}

The Projet San Francisco (PSF)/Center for Family Health Research (CFHR) is an accredited non-profit organization established in Kigali, Rwanda, in 1986 and is committed to the pursuit of excellence in research and service delivery to improve family planning and LARC. PSF/CHFR will oversee all in-country implementation activities.

We will implement the PPFP intervention in 12 intervention facilities with high-volume labor and delivery (L&D) departments and will use our 5 pilot facilities as training sites in Kigali. These 17 facilities include 15 health centers (which provide antenatal care [ANC], family planning, and infant vaccination [IV] and refer L&D cases to adjoining hospitals) and 2 stand-alone hospitals (which provide routine L&D services and also receive referrals of high-risk and complex obstetric cases from health centers). The selected facilities are currently staffed with roughly 443 facility-affiliated CHWs, 35 ANC nurses, 188 L&D nurses/midwives, 41 family planning nurses, and 41 IV nurses. Additionally, over a 3-month period, these facilities serve roughly 4657 ANC clients, 4196 L&D clients, and 4371 IV clients. All facilities have the infrastructure for PPFP provision and procurement; though no formal PPFP initiatives are currently taking place, PP implant insertions are infrequent, and no providers are trained to insert PPIUDs. Our team has worked in these clinics (conducting clinic logbook data abstraction, implementing couples’ HIV counseling and testing, implementing interval LARC services, and surveying providers and patients) for over 10 years [6, 14–21].

### Eligibility criteria {10}

Aim 1: Provider and stakeholder in-depth interviews

All participants will be government employees of at least 18 years of age who provide written informed consent to participate in in-depth interviews.

Aim 2: Implement PPFP services in a cluster-randomized stepped-wedge trial

Eligible PPFP providers will be women working in L&D or family planning at one of the study facilities. Eligible Happy Client promotors will be postpartum women who received promotions and selected a PPFP method. Eligible nurse and CHW promotors will be women working as nurses or CHWs at one of the intervention facilities. All women eligible for PPFP services in this study will be at any stage of pregnancy or up to 14 weeks postpartum and receiving ANC, L&D, IV, or postpartum services at one of the intervention facilities.

Aim 3: Client/couple, provider, and stakeholder in-depth interviews

All participants will be at least 18 years of age who provide written informed consent to participate in the in-depth interviews. Clients/couples will be those who received PPFP counseling. Providers and stakeholders will be government employees.

### Who will take informed consent? {26a}

Informed consent will be obtained from in-depth interview participants by trained study staff prior to the interview. Aim 1 interviews will be held during year 1 of the study, while the aim 2 interviews will take place 9 months after receiving PPFP promotions for PPFP clients and at the end of year 4/beginning of year 5 for stakeholder and provider interviews.

### Additional consent provisions for collection and use of participant data and biological specimens {26b}

This protocol received a waiver of consent for service delivery activities from the Emory and Rwandan Institutional Review Boards (IRBs). This trial does not involve collecting biological specimens.

## Interventions

### Explanation for the choice of comparators {6b}

A standard of care control was selected since it is the current alternative to offering the PPFP intervention. The stepped-wedge design will ensure that each facility receives the intervention over time and provides its own standard of care control. Facilities are high-volume and have similar client volume and staffing-to-patient ratios.

### Intervention description {11a}

We are evaluating a supply-demand intervention in a clinic-randomized design. The trial methods are provided here.

#### Organizational readiness checklist

Guided by the Consolidated Framework for Implementation Research (CFIR) [9, 10], we will conduct facility needs assessments to understand the readiness and barriers to intervention implementation. Checklists will measure facility volume and staffing, pharmacy capacity, physical space for the PPFP intervention, current contraception workflows and procurement systems, prior PPFP trainings, PPFP stocks, and any procedures (i.e., PPFP counseling tools or data collection systems) supporting PPFP supply or demand. Each assessment will take 1 h and will be conducted by trained research staff.

#### In-depth interviews

To explore the barriers to intervention implementation, we will conduct one-on-one in-depth interviews with *n* = 12 facility directors, *n* = 24 nurses in charge of L&D and family planning (2/facility), *n* = 24 CHW (2/facility), and *n* = 5 MOH stakeholders. CFIR provides guidance for qualitative semi-structured interview constructs [10]. Interviews will take 30 min, and participants will be compensated. Interview guides will be translated into the primary local language (Kinyarwanda) and pre-tested. Interviews will be anonymized and conducted by the research staff experienced in leading in-depth interviews.

#### PPFP service delivery training

The 5 pilot facilities (which are not randomized) will serve as sites to train and mentor nurses and midwives working in L&D and family planning at the 12 intervention facilities. The training will include a 2-day didactic session covering PPFP provision, follow-up, and use of the PPFP counseling flipchart to promote all PPFP method options (PPLARC, injectables, pills, etc.); mock counseling sessions; and PPIUD and PP implant insertion and removal trainings. Pre/post-training tests will consist of 10 true/false questions. Re-training will be offered after 1 week for trainees who fail to score > 80% on the post-training evaluation. After passing the didactic training, nurses and midwives who will be charged with insertions will be required to correctly insert 5 PPIUDs and 5 PP implants under supervision to be PPFP certified. The PPIUD insertions must include at least one of each of the following timings (which require different insertion techniques): immediate post-placental (within 10 min of placental delivery), 10 min to 48 h postpartum, and 4–14 weeks post-delivery.

#### PPFP demand creation training

We will train the government clinic staff in family planning, ANC, L&D, and IV to promote PPFP at the selected facilities. Trainings will comprise a 3-h-long didactic session led by the trained research staff followed by two supervised counseling sessions. CHWs from the health centers in charge of pregnant women and newborn health will receive a 1-day training on the PPFP flipchart. If interested in PPFP, women will be referred to the facility by their CHW. We will develop training materials to coach Happy Clients to discuss their own experiences with PPFP and address common concerns (as identified in our formative work and also addressed in the promotional flipchart). Happy Clients will be distributed equally across intervention facilities, affiliated with only one facility, and will be partnered with trained PPFP counselors. Finally, we will create an educational video in which a nurse counselor describes the PPFP flipchart information, visually shows each PPFP option, and men and Happy Clients give brief testimonies as to their experiences with different PPFP methods. Videos providing PPFP information will be shown in the ANC, L&D, and IV waiting areas in intervention facilities.

#### Stakeholder engagement

We will regularly engage stakeholders by presenting interim findings at quarterly Family Planning Technical Working Group meetings.

#### Follow-up procedures

PPFP follow-up appointments will be scheduled 6 weeks after insertion to correspond with the first IV visit. Women will be asked to self-report the side effects including signs of infection, and for PPIUD users, IUD string placement will be checked via bimanual pelvic exam. IUD strings will be trimmed as needed and a pelvic ultrasound given if the strings are not visible during physical exam. Women may decide to discontinue or request a new family planning method of their choice at any time.

#### Reimbursements

Using the performance-based financing (PBF) system used by the Rwanda Ministry of Health as a guide [22], providers will be reimbursed for PPFP methods inserted, and these payments will be made to their facility and included in addition to their regular PBF pay. For context, providers receive PBF pay of US $0.60/new contraceptive method user regardless of method type, and the average salary for nurses working in family planning or L&D is US $124–364/month, depending on the educational level. CHW and Happy Clients will be reimbursed for their work.

### Criteria for discontinuing or modifying allocated interventions {11b}

There will be no special criteria for discontinuing or modifying allocated interventions.

### Strategies to improve adherence to interventions {11c}

We will re-train providers in relevant service provision and promotional activities as needed.

### Relevant concomitant care permitted or prohibited during the trial {11d}

All side effects or incidental findings (for example, from any needed pelvic or ultrasound exam) will be shared with participants and their government health facility provider so that standard care treatments may be provided by the health facility.

### Provisions for post-trial care {30}

All clinical care including management of PPFP side effects will be provided by government facility personnel at health centers as part of usual care at no cost to the patient or health facility.

### Outcomes {12}

RE-AIM will guide outcome assessment (Table 1).

**Table 1 Tab1:** RE-AIM domains and measures

Domains	Outcome measures	Data source
**Reach**	^a^Stakeholders engaged and PPFP providers/promoters trained	Advocacy and training study log
	^a^Couples/clients receiving information about PPFP	PPFP logbook
**Effectiveness**	^a^Clients receiving PPFP/PP LARC methods PPFP side effects	PPFP logbook
**Adoption**	^a^Providers/promoters providing PPFP	Advocacy and training study log
**Implementation**	Provider/promoter time to provide PPFP Patient wait times to receive PPFP Implementation fidelity	Time motion studies, fidelity checklist
**Maintenance**	Woman/couple-level: continued PPFP use at 9 months, factors associated with PPFP uptake and continued use	Interviews, PPFP logbook
	Provider/facility-level: progress toward institutionalizing PPFP, factors associated with PPFP continued provision at the end of implementation	Interviews, standardized checklist
	Stakeholder-level: progress of the Ministry of Health to nationalize PPFP services at the end of implementation	Interviews

^a^Quantitative outcomes used in power analyses, see Table 5

#### Reach and adoption

Data on the number and proportion of stakeholders engaged, providers trained, and promoters trained will be abstracted from the advocacy and training study logs. Data on the number and proportion of couples/clients receiving information about PPFP will be abstracted from PPFP logbooks.

#### Effectiveness

Data on the number and proportion of clients receiving PPFP/PPLARC methods and experience of side effects will be abstracted from PPFP logbooks.

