#### Safety endpoints

PPFP side effects include pelvic pain, heavy menstrual bleeding/menorrhagia, dysmenorrhea, infection, perforation of the uterine wall, pelvic inflammatory disease (PID), headaches, irregular periods, nausea, blood clot, minor bleeding, severe bleeding, and pain.

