## Data collection and management

### Plans for assessment and collection of outcomes {18a}

The number of stakeholders engaged and providers trained and certified will be recorded in an Advocacy and Training logbook. CHW counseling activities will be measured on referral slips which will record if a male partner was present. Women/couples receiving one-on-one PPFP counseling will have their method of interest, whether a male partner was present, household income, and estimated date of delivery recorded in a PPFP logbook, developed by the study team during the pilot and maintained by government clinic staff. The PPFP logbook will also record PPFP uptake and, among PP LARC users, provider perception of ease of insertion, client anxiety during insertion, and client pain during insertion (scales of 1–10). During follow-up visits, the PPFP logbook will record PPFP side effects and method failures. Facility information, client’s age, and parity will be abstracted from government Family Planning logbooks.

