### Plans to promote participant retention and complete follow-up {18b}

Aim 1/2: In-depth interviews: As these are one-time interviews, there is no retention plan.

Aim 2: Implement PPFP services in a clinic-randomized stepped-wedge trial: To increase attendance at PPFP follow-up appointments at one of the intervention facilities, we will reimburse women for their transportation/childcare costs for follow-up visits. To increase follow-up, we will also provide CHWs with lists of clients in their catchment areas who are pending follow-up to remind those women about their appointments.

Any identification of participation or follow-up rates that represent threats to our ability to sufficiently answer the research questions will be met with action by the PI to intervene to remedy the shortcomings.

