### Data management {19}

PPFP logbooks will be maintained by trained PPFP providers in government facilities. Logbook data will be extracted into tablets weekly by the research field team through the mobile data collection platform Survey CTO v2.41 (Dobility, Cambridge, USA). Survey CTO data will be downloaded for weekly query and cleaning in a Microsoft Access database. Data will then be imported into SAS (Cary, NC) for analysis. A unique code will track clients from the community through ANC, L&D, and IV. This unique code is composed of personal information that the participant would remember (e.g., the first three letters of the mother’s name) but is unlinked to identifiers. We used this code in our previous pilot and were able to track > 95% of women who attended multiple visits at ANC, delivery/postpartum, and/or infant vaccination. For qualitative assessments, de-identified transcribed audio recordings will be stored on a secure server. Recruitment and missing data reports will be monitored weekly by the study coordinator, the PI, and the study statistician.

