#### Descriptive analyses

Descriptive analyses will evaluate the outcomes of PPFP uptake (by method type), follow-up attendance, side effects (by method type), and client satisfaction. We will assess the association between PPFP uptake and timing of counseling (chi-square test), presence of a male partner (chi-square test), and the number of counseling sessions received (chi-square test for trend).

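### The side-effect outcome names only the PPFP logbook as its source, so a serious event held only in the separately abstracted adverse event records could be left out of its count

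*Protocol article*

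**What the plan says.** Under Outcomes {12}, the Effectiveness row of Table 1 lists "Clients receiving PPFP/PP LARC methods PPFP side effects" and gives the PPFP logbook as the data source. The Effectiveness paragraph repeats this: "experience of side effects will be abstracted from PPFP logbooks". Plans for assessment and collection of outcomes {18a} says when the entries are made: "During follow-up visits, the PPFP logbook will record PPFP side effects and method failures". The scheduled visit is 6 weeks after insertion (Follow-up procedures).

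Adverse event reporting and harms {22} describes another route. Facility staff record AEs and SAEs in pre-existing government clinic logbooks, events also go on a study adverse event log, and research staff later abstract these data electronically. Perforation, PID and menorrhagia lead to specialist referral.

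The outcome bears on an expectation stated in Objectives {7}, "We expect PPFP client satisfaction will be high, and side effects will be rare". Its analysis is set out under Descriptive analyses: "Descriptive analyses will evaluate the outcomes of PPFP uptake (by method type), follow-up attendance, side effects (by method type), and client satisfaction".

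**The concern.** The event types on the two routes overlap. Infection, perforation, PID, heavy bleeding and blood clots appear both in the Safety endpoints list of side effects and in the AE section. Nothing in the article brings the AE records into the outcome.

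An outcome abstracted from one book cannot contain an event that the book does not hold. A woman who misses her visit and is later treated for PID, or who is referred to a specialist for a perforation, may have an AE entry and no side-effect entry in the PPFP logbook. Missed visits are foreseen: Plans to promote participant retention {18b} provides transport and childcare reimbursement and community health worker reminders "To increase attendance at PPFP follow-up appointments at one of the intervention facilities".

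What is at stake is the published count of serious side effects by method. It could be lower than the count in the trial's own adverse event log, in a programme that expects side effects to be rare and is intended to inform national roll-out.

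**Working it through.** The point disputes no sample size, power or alpha figure, so there is no stated figure to reproduce. The check compares sections and then gives a sense of scale.

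**Comparison of sections**

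- Source named for the outcome: PPFP logbook (Table 1; Effectiveness paragraph). Elsewhere in Table 1, where two sources are meant, both are listed; one Maintenance row gives interviews and the PPFP logbook.
- Other records of the same event types: government clinic logbooks and the study AE log ({22}). The PPFP logbook was developed by the study team ({18a}). The clinic logbooks in {22} already exist and hold the incident, actions taken and supervisor notes. The article uses the term clinic logbook loosely in places, so some overlap between the books is possible. The study AE log is clearly separate.
- Link between the routes: none is described for this outcome.

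**Scale, PPIUD only**

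Inputs from the article: 3687 expected PPIUD insertions (Sample size {14}), and serious copper-IUD rates of 5% infection, 1.6% perforation, 0.5% PID and 0.2% menorrhagia ({22}).

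- 3687 × 0.05 = 184.4
- 3687 × 0.016 = 59.0
- 3687 × 0.005 = 18.4
- 3687 × 0.002 = 7.4
- Sum: 269.2 events, or 7.30% of insertions, if the events do not overlap.

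Assumptions, none of them in the article: follow-up attendance A; equal event risk in attenders and non-attenders; every attender's event is in the PPFP logbook; and a share c of non-attenders' events is in the AE records and not in the PPFP logbook.

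- Logbook alone = 269.2 × A
- Logbook plus AE records = 269.2 × (A + (1 − A) × c)

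| A | Logbook alone | Both, c = 0 | Both, c = 0.5 | Both, c = 1 |
|---|---|---|---|---|
| 0.9 | 242.2 (6.57%) | 242.2 (6.57%) | 255.7 (6.94%) | 269.2 (7.30%) |
| 0.8 | 215.3 (5.84%) | 215.3 (5.84%) | 242.2 (6.57%) | 269.2 (7.30%) |

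Percentages are per insertion. The count missing from the logbook is 0, 13.5 or 26.9 events at A = 0.9, and 0, 26.9 or 53.8 at A = 0.8.

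**Denominator**

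With attenders as denominator, the logbook rate is 269.2 × A / (3687 × A) = 7.30% at any A, so under equal risk only the count is low. If women with problems return more often than others, the attender rate overstates. Descriptive analyses states no denominator.

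The same arithmetic shows why a per-insertion rate should not stand alone. Even with both sources it is at most 7.30%, and it falls below the attender rate whenever c is less than 1.

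Mild side effects are self-reported at follow-up. Per insertion, the article's 12% pelvic pain would read 12 × 0.9 = 10.8% or 12 × 0.8 = 9.6%, so these belong among attenders.

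**The case against.** The strongest reply is that two records for two purposes is ordinary practice. The article names a source for a RE-AIM measure and, separately, a route for safety reporting. It does not say that the first excludes the second, and reconciliation may be set out in the manual of operating procedures, the SOPs or an analysis plan that is not shown. Facility staff maintain the PPFP logbook and also collect AEs, so an event may be entered in both. The reference to follow-up visits is not confined to the 6-week appointment, so a woman who returns late with a complication could still be logged.

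Most of this stands, and it limits the point. It does not remove it: the article names a source, twice, that is narrower than the data it says the trial will abstract.

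A reader might go further in three ways that the article does not support.

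- That events in the AE records will not be counted. No section shows that any event would be known only from those records.
- That the error can run only towards side effects looking rare. This holds for the count, or for a per-insertion rate. For a proportion among attenders the bias may be nil or in the other direction.
- That safety monitoring is weakened. AEs and SAEs have their own interim analysis ({21b}), which names no data source. Under {22} the AE log goes to the IRBs and NIH, and the statistician prepares AE and SAE listings for the monitoring body.

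**Conclusion.** The point holds in a limited form, as a minor one. The source named for the descriptive side-effect outcome is narrower than the event data the trial will already hold, so a serious event recorded only as an AE could be missing from the outcome's count.

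The size cannot be derived from the article and may be zero. The illustrative range is 0 to about 27 of 269 serious PPIUD events at 90% attendance, and 0 to about 54 at 80%. It rests on the article's background rates without overlap, equal risk by attendance, and assumed attendance and AE capture. The direction for a proportion is open until a denominator is fixed. The outcome is not among those marked for the power analyses, and no test or stopping decision is tied to it.

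**What to change.** In Table 1 and the Effectiveness paragraph, add the AE records (government clinic logbooks and study AE log) as a second source for serious side effects: infection, perforation, PID, menorrhagia, blood clot and severe bleeding. Then:

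- Count an event found in either source.
- De-duplicate by the client code described in Data management {19} ("A unique code will track clients from the community through ANC, L&D, and IV") where it is carried on the AE record, and otherwise by facility, date, method and event.
- Report counts by method and by source.
- Show the serious rate per insertion, labelled a minimum because a non-attender with no AE record counts as event-free, beside the PPFP-logbook rate among follow-up attenders, with the attendance rate.
- Keep mild self-reported side effects among attenders.

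The cost is one line in each of two places and some linkage of data that are abstracted anyway. An identifier must be carried on the AE records, which the article does not say will happen. Reported serious counts may be slightly higher.
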